**Methods: Assignment of interventions (for controlled trials)**

**Allocation:**

***SPIRIT Guidance: Sequence generation***

*16a Method of generating the allocation sequence (eg, computer-generated random numbers), and list of any factors for stratification. To reduce predictability of a random sequence, details of any planned restriction (eg, blocking) should be provided in a separate document that is unavailable to those who enroll participants or assign interventions*.

Participants will be randomized, maintaining concealment of allocation sequence, using a computer-generated random number list of variable block size into multiple intervention groups (and an observation only group will emerge from those not consenting to randomization). Stratification for age will be used initially to ensure that groups remain balanced in size and prognosis.

***SPIRIT Guidance: Allocation concealment mechanism***

*16b Mechanism of implementing the allocation sequence (eg, central telephone; sequentially numbered, opaque, sealed envelopes), describing any steps to conceal the sequence until interventions are assigned*

***SPIRIT Guidance: Implementation***

*16c Who will generate the allocation sequence, who will enrol participants, and who will assign participants to interventions*

Randomization sequence was created using Sealed Envelope Ltd 2019 and was stratified by study center and age using random block sizes of 28 and 42 sizes into seven treatments (11). Before randomizing, recruiting physician will confirm eligibility and obtain written informed consent from the participant. Upon entering participant’s demographic details in the IT module, a unique patient ID for the said center and treatment arm would be allocated automatically meaning the recruiting physician has no control over assigning intervention.

***SPIRIT Guidance: Blinding (masking)***

*17a Who will be blinded after assignment to interventions (eg, trial participants, care providers, outcome assessors, data analysts), and how*

*17b If blinded, circumstances under which unblinding is permissible, and procedure for revealing a participant’s allocated intervention during the trial*

Not Applicable

**Methods: Data collection, management, and analysis**

***SPIRIT Guidance: Data collection methods***

*18a Plans for assessment and collection of outcome, baseline, and other trial data, including any related processes to promote data quality (eg, duplicate measurements, training of assessors) and a description of study instruments (eg, questionnaires, laboratory tests) along with their reliability and validity, if known. Reference to where data collection forms can be found, if not in the protocol*

*18b Plans to promote participant retention and complete follow-up, including list of any outcome data to be collected for participants who discontinue or deviate from intervention protocols*

**6 DATA COLLECTION, MANAGEMENT AND ANALYSIS**

The COVID-19 PATIENTS RESEARCH PORTAL (IT Module) is an electronic case reporting form (CRF) developed by IT Department of University of Health Sciences, Lahore and accessible via <theprotect.com.pk>. It is expected to fully facilitate both investigators as well study participants. Using a computer desktop or any portable device such as personal computers and tablets, it allows input of data directly from patients’ bedsides for facilities that are electronically equipped and offer reliable internet within isolation areas. It was finalized after pilot testing at six study centers. Considering the highly contagious nature of this disease, the electronic CRF is expected to minimize cross-infection possible with use of printed study tools. The IT module has the option for investigators to withdraw a case should a participant wishes to discontinue enrollment in the study at any point of time.

***SPIRIT Guidance: Data management***

*19 Plans for data entry, coding, security, and storage, including any related processes to promote data quality (eg, double data entry; range checks for data values). Reference to where details of data management procedures can be found, if not in the protocol*

The role of IT Manager has been assigned to any member of the site team or his/her nominee. (S)he will have exclusive access to the data entry module under given terms of use to ensure data protection and privacy. Data will be entered immediately upon receipt. Sites are trained to develop a housekeeping system to keep track of local data including date stamping all documents on receipt. For data completion and validation, consistency checks would be performed during entry and warning(s) (if any) will be displayed. Data will be copied on a different server regularly. In case of an erroneous entry, the IT Manager will contact designated IT resource at UHS or Lead Biostatistician, provide the justification and get the issue resolved. Each of such correction request would be recorded.

***SPIRIT Guidance: Statistical methods***

*20a Statistical methods for analyzing primary and secondary outcomes. Reference to where other details of the statistical analysis plan can be found, if not in the protocol*

*20b Methods for any additional analyses (eg, subgroup and adjusted analyses)*

*20c Definition of analysis population relating to protocol non-adherence (eg, as randomized analysis), and any statistical methods to handle missing data (eg, multiple imputation)*

All trial data will be analyzed by biostatistician based at the University of Health Sciences, Lahore, using an a priori, approved analysis plan (SPSS 25.0). Interim analyses at each stage (first stage will be 10% of the total sample size) of the adaptive design will be pre-planned and undertaken confidentially keeping investigators and participants blind till the end of the trial. Primary and secondary outcomes will be analyzed in accordance to the group in which the participants were randomized deploying the intention-to-treat principle. The primary analysis will be expressed as odds ratio (OR) of the comparison between groups for the primary outcome. Interim analyses will be conducted without disclosing groups, thereby maintaining a level of blinding in interpretation of interim results. The confidential interim analyses at each stage of the adaptive design will examine for imbalance in co-morbidity at baseline. If any differences are observed then stratification may be modified confidentially. The results will be reported as point estimates and 95% confidence intervals. Secondary analysis will include in time-to-event data to directly compare the data among groups with survival plots and hazard ratios. This will permit evaluation of the decision to continue beyond Day 7 of treatment upon testing negative, potential drug effects besides informing valuable understanding of drug effectiveness. Stratified analyses will be done by baseline COVID-19 positive status upon testing and age groups. Multiple regression and Cox proportional hazards stratified analysis will be used to adjust for a small number of covariates taken from stratification factors if there were baseline imbalances. Secondary analyses will deploy multiple regression models as well Chi square, Fisher’s exact test and one-way ANOVA to compare groups. The two-sided p-value less than or equal to 0.05 will be taken as significant. Imputation method will be used to handle missing data.

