**Abstract**

Objectives

To evaluate the effectiveness of Hydroxychloroquine Phosphate/Sulfate (200 mg orally 8 hourly thrice a day for 5 days) *versus* oseltamivir (75 mg orally twice a day for 5 days) *versus* Azithromycin (500 mg orally daily on day 1, followed by 250 mg orally twice a day on days 2-5) alone and in combination (in all seven groups), in clearing the coronavirus (COVID-19) nucleic acid from throat and nasal swab and in bringing about clinical improvement on day 7 of follow-up (primary outcomes).

Trial Design

An adaptive design, set within a comprehensive cohort study, is chosen because it permits flexibility in this fast-changing clinical and public health scenario. The randomized study will be a multicenter, multiarm, multistage, randomized controlled trial with a parallel design. An observation only cohort will emerge from those not consenting to randomization.

Participants

Eligible will be newly diagnosed patients, either hospitalized or in self-isolation, without any comorbidities or with controlled chronic medical conditions like diabetes mellitus and hypertension. Participants of any gender or age group having tested positive for COVID-19 on Real-Time qRT-PCR (Quantitative Reverse Transcription PCR) will be invited to take part in study at twelve centers across nine cities in Pakistan. Those pregnant or lactating, severely dyspneic or under respiratory distress, already taking a treatment, and with serious co-morbidities like liver or kidney failure will be excluded.

Intervention and Comparator

A total of seven comparator groups will be formed: Each drug (Hydroxychloroquine Phosphate/Sulfate, Oseltamivir and Azithromycin) given as monotherapy (three groups); combinations of each of two drugs (three groups); and a final group on triple drug regimen.

Main Outcomes

The laboratory-based primary outcome will be turning test negative for COVID-19 on qRT-PCR on day 7 of follow-up. The clinical primary outcome will be improvement from baseline of two points on a seven-category ordinal scale on day 7 of follow-up.

Randomization

Participants will be randomized, maintaining concealment of allocation sequence, using a computer-generated random number list of variable block size into multiple intervention groups.

Blinding

Computerized allocation to treatment group will be done upon adding participants demographic details and confirmation of informed consent. Neither physician nor participants will be blinded.

Sample Size

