***SPIRIT Guidance: Sample size***

*14 Estimated number of participants needed to achieve study objectives and how it was determined, including clinical and statistical assumptions supporting any sample size calculations*

This is an adaptive design and parameters for formal sample size calculation in a new disease of a previously unknown virus are not available. Then the sample size and power analysis are indicative for review at each stage of adaptive design. In a standard two-arm, head-to-head trial, the sample size would have been as follows: in order to detect a difference in the laboratory-based primary outcome of 10% (assuming a 50% of participants receiving Hydroxychloroquine Phosphate/Sulfate turn test negative at day 7 and expected rates in comparator groups of 60%), at a significance level 5% and a power of 90%, a sample size of approximately 520 subjects in each group will be required. This sample size will be enough to detect a small-medium difference (Cohen’s d 0.3, a significance level 5% and a power of 90%) in the clinical primary outcome. Additional considerations will need to make for the interim analysis at every stage of the adaptive design. Interim analysis will review sample size according to time to clearance also. Planned blinded sample size re-estimations will need to be undertaken in which we will constantly re-examine the original sample size assumptions. We will aim to maintain the trial power at 90% even if the original sample size assumptions turn out to be far from the observed data. The adaptation at each stage will allow us to drop out fewer promising interventions and will prevent an underpowered trial for the most promising interventions. As the planned modifications will be undertaken in a blinded fashion, there will be no increase in the type I error rate.

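### The only covariate rule adjusts for stratification factors, and only on imbalance, so it omits the baseline ordinal category on which the clinical primary outcome is scored and gives up some precision

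*Protocol*

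**What the plan says.** The Abstract (Main Outcomes) defines the clinical primary outcome as "improvement from baseline of two points on a seven-category ordinal scale on day 7 of follow-up". The Statistical methods section (SPIRIT item 20) expresses the primary analysis as an odds ratio and names no covariates for it. Later in the same section, multiple regression and stratified Cox models are to "adjust for a small number of covariates taken from stratification factors if there were baseline imbalances".

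The Implementation section (item 16c) says the randomization was "stratified by study center and age using random block sizes of 28 and 42 sizes into seven treatments"; Sequence generation (item 16a) mentions age only. Item 20 also plans stratified analyses by baseline test status and age group, and an interim check for imbalance in co-morbidity. Baseline ordinal category appears in none of these places.

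The Outcomes section (item 12) schedules the ordinal scale on days 3, 5, 7, 9, 11 and 14. It lists no day 0 assessment.

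**The concern.** Whether a patient can move two categories in seven days depends on where that patient starts. On a bounded scale, someone within one category of the best score cannot move two. The trial takes both hospitalized and home-isolated patients, so starting categories should differ. Baseline category is therefore a natural candidate for a strong predictor of the clinical primary outcome.

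The rule has two weaknesses. It restricts the source of covariates to factors chosen for randomization, which excludes the one baseline value the endpoint is built on. It also makes adjustment depend on an observed imbalance, although a prognostic covariate improves precision whether or not the arms happen to differ. What is at stake is precision in the clinical comparison, most of all where arms are small. Deciding on adjustment after seeing the data also leaves an avoidable choice open in an open-label trial.

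**Working it through.** **1. The Protocol's own figures.** The Sample size section (item 14) works from "assuming a 50% of participants receiving Hydroxychloroquine Phosphate/Sulfate turn test negative at day 7 and expected rates in comparator groups of 60" per cent and concludes that "at a significance level 5% and a power of 90%, a sample size of approximately 520 subjects in each group will be required". Item 20 sets the test: "The two-sided p-value less than or equal to 0.05 will be taken as significant". Equal allocation is inferred from equal group sizes and from blocks of 28 and 42, both multiples of seven.
- Laboratory outcome, 50% v 60%, two-sided 5%, 90% power, pooled variance: 519 per group; power at 520 is 90.1%. The stated 520 reproduces.
- Clinical outcome, for which item 14 states Cohen's "d 0.3, a significance level 5% and a power of 90" per cent: 234 per group would be enough, and 520 per group gives 99.8% power.

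The 10-point difference thus belongs to the laboratory outcome. The clinical outcome has d 0.3.

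**2. Adjustment on the d scale.** If the correlation between baseline and outcome is ρ, the residual variance is multiplied by 1 − ρ². For ρ = 0.3, 0.5 and 0.7:
- 520 per group: power rises from 99.8% to 99.9% or more, a gain of at most 0.2 points.
- The n for 90% power falls from 234 to 213, 176 and 120.

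The outcome as defined is a responder outcome, so the next step works on that scale.

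**3. Translating d 0.3 to a responder difference.** From 50%, a normal latent scale gives Φ(0.3) = 62%. A logistic one gives an odds ratio of exp(0.3π/√3) = 1.72, or 63%. I take 50% v 62.5%, a 12.5-point difference.

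**4. Assumed strength of baseline category.** The documents give no association, so these are assumptions. Three baseline categories hold 30/50/20% of patients. Comparator response by category (comparator overall rate 43% to 48%):
- weak: 35/50/60% (R² 3%);
- moderate: 20/50/75% (R² 15%);
- strong: 8/50/80% (R² 27%).

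R² is the between-category variance over the total binary variance.

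**5. Formulas** (n per arm; overall rates p_c, p_t; category share w_k with rates p_k, q_k; common conditional log odds ratio b, solved to give the 12.5-point overall difference).
- Unadjusted: log OR = logit(p_t) − logit(p_c), with variance 1/[n p_c(1 − p_c)] + 1/[n p_t(1 − p_t)].
- Adjusted: 1/Var(b) = Σ_k 1/{1/[n w_k p_k(1 − p_k)] + 1/[n w_k q_k(1 − q_k)]}.
- Power = Φ(estimate/SE − 1.96). Efficiency = (adjusted z / unadjusted z)².

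Example, moderate, 150 per arm: unadjusted 0.504/0.233 = 2.16, power 58%; adjusted 0.596/0.255 = 2.34, power 65%; efficiency (2.34/2.16)² = 1.17.

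**6. Results, unadjusted v adjusted power, 12.5-point difference.**

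| n per arm | weak | moderate | strong |
|---|---|---|---|
| 520 | 98.1 v 98.4% | 98.1 v 99.2% | 98.0 v 99.7% |
| 150 | 58 v 59% | 58 v 65% | 58 v 72% |
| 67 | 30 v 31% | 30 v 35% | 30 v 40% |

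The efficiency gain is about 3%, 17% and 39%. The 67 is 470/7, from the Trial Status figure of about 470 recruited, if all were randomized and spread evenly. The 150 is an assumed intermediate size.

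**7. Smaller effect.** With a 10-point difference, power at 520 per group is 90 v 91%, 90 v 94% and 90 v 97%; at 150 per arm it is 41 v 42%, 41 v 47% and 41 v 53%.

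**8. What adjustment does to the odds ratio.** For a 10-point difference the marginal odds ratio is 1.5, and the conditional one is 1.52, 1.61 or 1.76 (weak, moderate, strong).

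**The case against.** The best defence is that item 20 never says the primary odds ratio excludes baseline category. The sentence on covariates follows the secondary time-to-event and stratified analyses, so it can be read as a supplementary rule. The next sentence allows multiple regression with unstated covariates, and an approved analysis plan is cited but not shown. A reader might infer that baseline category can never enter the primary comparison; the documents do not support that. What stands is narrower: the one rule the Protocol does state limits the source of covariates and waits for imbalance. A plan that put baseline category in the primary model would depart from that rule, and the unspecified regressions belong to the secondary analyses.

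Three other stronger readings also fail.
- **Bias.** Chance differences in starting severity do not bias an unadjusted odds ratio under randomization. The confidence interval and type I error already allow for them. The cost is precision.
- **A material power loss at the planned size.** Figures for a 10-point difference borrow the laboratory effect. At d 0.3 and 520 per group there is almost nothing left to gain.
- **A baseline score already on file.** The outcome definition requires one, but item 12 lists no day 0 score. If day 3 served as baseline it would be post-treatment and unsuitable as a covariate.

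It is also fair to say that excluding severely dyspneic patients narrows the baseline range and may weaken the predictor. In the weak case the gain is only about 1 point at any arm size. The limit on improvement, however, acts at the mild end of the scale, and those patients remain eligible.

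**Conclusion.** The point holds as a matter of efficiency and prespecification; it does not make the analysis invalid. The stated rule omits the baseline value on which the clinical primary outcome is defined and ties adjustment to observed imbalance, which is the wrong trigger for a precision gain.

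Its size rests on assumed category shares and response rates. The loss is negligible at the Protocol's clinical effect with 520 per group. It matters if arms are much smaller or the true effect is below d 0.3. Neither is remote: item 14 calls its sample size indicative, recruitment stood at about 470 in July 2020, and the design takes interim looks and may drop arms on fewer patients than the final number.

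**What to change.** In Statistical methods (item 20), state that the primary model for the clinical outcome includes the pre-treatment baseline ordinal category as a categorical covariate in every comparison, whether or not imbalance is seen. Report the unadjusted odds ratio as a supporting analysis. In Outcomes (item 12), add day 0 to the listed days for the ordinal scale, so that a post-treatment day 3 score is not used as the baseline.

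The cost is a sentence and a model term, plus a day 0 score that the outcome definition already requires. The real downside is the change of target. The adjusted odds ratio is conditional on baseline category and lies further from 1 (about 1.5 to 1.8 against a marginal 1.5 for a 10-point difference). The plan must therefore say which of the two is the primary estimate and label both.

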***Inclusion Criteria***

1. Confirmed SARS-CoV-2 (COVID-19) infection by a positive test result
2. Either gender
3. Symptomatic for example fever, dry cough, myalgias

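### The adjustment rule takes covariates only from the stratification factors and only after imbalance is seen, so days since symptom onset falls outside it and a precision gain of unknown size is forgone

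*Protocol*

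**What the plan says.** - **Entry.** Under Inclusion Criteria a participant needs a positive test and must be "Symptomatic for example fever, dry cough, myalgias". The eligibility text adds that patients are newly diagnosed, which limits time since diagnosis but not time since onset. Neither the inclusion nor the exclusion list sets a maximum symptom duration.
- **Stratification.** Under Implementation (item 16c) the randomisation sequence "was stratified by study center and age". Sequence generation (item 16a) names age only.
- **Adjustment.** Under Statistical methods (item 20), multiple regression and stratified Cox analysis are to "adjust for a small number of covariates taken from stratification factors if there were baseline imbalances". The primary result is an odds ratio between groups. Stratified analyses are by baseline COVID-19 status and age group. Further regressions are listed as secondary analyses, with no covariates named.
- **Sample size (item 14).** The calculation is introduced by "In a standard two-arm, head-to-head trial, the sample size would have been as follows". Its inputs are "assuming a 50% of participants receiving Hydroxychloroquine Phosphate/Sulfate turn test negative at day 7" and "expected rates in comparator groups of 60" per cent, and it concludes that "at a significance level 5% and a power of 90%, a sample size of approximately 520 subjects in each group will be required". Item 20 adds: "The two-sided p-value less than or equal to 0.05 will be taken as significant".

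**The concern.** The laboratory primary outcome is read on a clock that starts at entry, not at onset. Someone who enrols late in the illness has had longer to clear the virus by day 7 of follow-up than someone who enrols early. Recruitment covers hospitalised and home-isolating patients, and the protocol notes that diagnostic facilities and admission criteria differ between cities. A wide spread of illness day at entry is therefore plausible.

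The protocol is not silent on covariates. It fixes a rule, and the rule is weak in two ways. It limits candidates to the stratification factors, which leaves out illness day. It also makes adjustment depend on the imbalance observed, whereas covariates are better chosen in advance for their prognostic value. An analysis plan that follows the rule gives up precision that costs no extra participants.

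**Working it through.** **1. Reproduce the planned size.** Inputs from item 14: 50% and 60%, 5% significance, 90% power. Item 20 makes the test two-sided. With pooled variance and mean rate 0.55:

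n = [1.960 × √(2 × 0.55 × 0.45) + 1.2816 × √(0.25 + 0.24)]² / 0.10² = 518.04, so 519 per group.

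This agrees with the stated figure of about 520. Power at 520 is 90.1%.

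**2. Unadjusted odds ratio at 520 per group.**
- Log odds ratio: ln(0.60/0.40) − ln(0.50/0.50) = ln 1.5 = 0.4055.
- Standard error: √[1/(520 × 0.25) + 1/(520 × 0.24)] = 0.1253.
- Ratio: 3.235. Power: Φ(3.235 − 1.960) = 89.9%.

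The 50% and 60% are marginal rates, so any effect of illness day is already averaged into them. The planned power stands without adjustment.

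**3. Adjusted analysis.** Neither the effect of illness day nor its spread is in the documents, so both are assumed. The model is logit P(negative at day 7) = a_t + b × x, with x (days since onset) uniform over 0 to L. The intercepts a_0 and a_1 are solved so that the average rates stay at 50% and 60%. The conditional log odds ratio is d = a_1 − a_0. Its standard error comes from the Fisher information for intercept, treatment and x, and power is Φ(d/SE − 1.960). The information ratio is (d/SE)² divided by 3.235².

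Worked case, L = 10 and b = 0.3: a_0 = −1.5, d = 0.478, SE = 0.1365, ratio 3.50, power Φ(1.54) = 93.8%.

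| Spread of onset | Slope b (odds ratio per day) | Conditional odds ratio | Information ratio | Adjusted power at 520 |
|---|---|---|---|---|
| 0-5 days | 0.1 (1.11) | 1.50 | 1.005 | 90.0% |
| 0-5 days | 0.2 (1.22) | 1.51 | 1.02 | 90.4% |
| 0-5 days | 0.3 (1.35) | 1.53 | 1.04 | 91.1% |
| 0-5 days | 0.4 (1.49) | 1.55 | 1.08 | 91.9% |
| 0-10 days | 0.1 (1.11) | 1.51 | 1.02 | 90.4% |
| 0-10 days | 0.2 (1.22) | 1.55 | 1.08 | 91.9% |
| 0-10 days | 0.3 (1.35) | 1.61 | 1.17 | 93.8% |
| 0-10 days | 0.4 (1.49) | 1.70 | 1.29 | 95.7% |

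Against 89.9% unadjusted, the gain is 0.1 to 2.0 points over 0-5 days and 0.5 to 5.8 points over 0-10 days. With b = 0 it is zero.

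**4. Check with another shape.** A normally distributed covariate with an assumed odds ratio of 1.25 to 3.0 per standard deviation gives adjusted power of 90.2% to 94.9%. The size needed for 90% power falls from 522 per group (unadjusted Wald test) to between 516 and 423, a saving of about 1% to 19%.

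**The case against.** The strongest reply is that this is an optional improvement of unknown and perhaps negligible size. Much of that stands. Both slope and spread are assumptions. Enrolling newly diagnosed patients may narrow the spread, and over 0-5 days the gain is at most 2 points. The steepest 0-10 day case implies clearance in the 50% group rising from 12% for entry on day 0 to 88% for entry on day 10, and nothing in the documents supports so steep a gradient.

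It can also be said that naming covariates belongs in the analysis plan, which the protocol mentions and which is not at hand. That would answer a complaint that onset time is not named. It does not answer the rule itself, which the protocol states and a consistent plan would follow.

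Some stronger readings are tempting but not supported:
- *That the trial falls below its planned power.* It does not, as step 2 shows.
- *That leaving onset time out biases the odds ratio towards 1.* The gap between 1.50 and the conditional values is non-collapsibility. The marginal 1.50 is a valid target and is the one the sample size assumes.
- *That onset time cannot enter any model.* The secondary regressions name no covariates, so the restriction lies in the stated adjustment sentence.
- *That both primary outcomes lose power.* Nothing was computed for two-point improvement on the ordinal scale, and the documents do not say how illness day acts on it.
- *That onset date is not collected.* The case report form is not shown and may already hold it.
- *That adjustment would rescue a trial that stops early.* The protocol expects at least three more months of recruitment, and plans to drop arms and re-estimate the sample size. How many participants each arm will reach is therefore a separate question.

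**Conclusion.** The point holds as a matter of efficiency. The protocol fixes an imbalance-triggered rule confined to center and age, while entry leaves symptom duration open. Days since onset is therefore outside the stated adjustment for a day-7 clearance outcome on which it plausibly bears. Validity and the planned 90% power are intact.

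For the laboratory outcome, the gain forgone runs from nothing to about 6 power points at 520 per group, and is at most about 2 points if onset spreads over no more than 5 days. The result rests on a uniform spread, a linear log-odds effect and the protocol's own marginal rates. The change is worth making because it is cheap and because the rule is a poor one even for center and age.

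**What to change.** In Statistical methods (item 20), replace the imbalance-triggered rule with: *The primary logistic model for day-7 PCR negativity adjusts for center, age and days from symptom onset to randomisation, pre-specified whatever the observed balance; the odds ratio is conditional on these covariates, and the unadjusted odds ratio is also reported.* The same may be applied to the clinical primary outcome.

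Confirm that the electronic case report form captures onset date. If it does not, add the field and complete it from case files for those already enrolled.

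**Cost.** Analysis wording and at most one date field, with no extra participants. There are three downsides:
- Onset date is recalled and may be missing for early participants. Imputation from baseline data only, or a missing-value category, handles this.
- The adjusted odds ratio is slightly larger than the marginal one (about 1.50 to 1.70 against 1.50 over the assumed range), so the effect measure must be stated.
- The change comes after about 470 open-label enrolments by 3 July 2020. It should be fixed, and documented as fixed, before any unblinded comparative results are seen.

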Secondary outcomes like Quality of Life and Symptoms Score will be recorded on day 0 and 7 using standardized tools such as World Health Organization Quality of Life Questionnaire (WHO QoL) and Wisconsin Upper Respiratory Symptoms Survey (WURSS) respectively (copies **attached)**. The former is expected to capture participant’s lived experience during care that has not been documented in literature to date. The latter is expected to indicate any respiratory co-infection including those acquired from the hospital. The investigators will also monitor and record variables including duration it takes to oxygenate and ventilate, duration stayed oxygenated and ventilate, number of hospitals stay days, admission to intensive care, and mortality. This methodology has been peer reviewed by an external expert **(see annex 1).** A GCP certified, experienced researcher will conduct the training of up to 50 investigators across 13 participating sites to prepare them for all aspects of this study.

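### Quality of life and symptom scores are recorded on day 0 and day 7, but the only stated covariate rule does not provide for the day-0 score and makes adjustment depend on observed imbalance

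*Protocol*

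**What the plan says.** Protocol, Outcomes (item 12): "Secondary outcomes like Quality of Life and Symptoms Score will be recorded on day 0 and 7 using standardized tools". The tools are WHO QoL and WURSS. Both constructs also appear in the Secondary Objectives (2.1).

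Protocol, Statistical methods (item 20): "Secondary analyses will deploy multiple regression models as well Chi square, Fisher’s exact test and one-way ANOVA to compare groups". The sentence does not say which method goes with which outcome, or whether a score is compared at day 7 or as change from day 0.

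The sentence before it gives the section's only covariate rule. Multiple regression and stratified Cox analysis are to "adjust for a small number of covariates taken from stratification factors if there were baseline imbalances".

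Protocol, Implementation (item 16c): the randomisation sequence "was stratified by study center and age using random block sizes of 28 and 42 sizes into seven treatments". Sequence generation (item 16a) mentions age only. Neither place makes a baseline score a stratification factor.

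The Statistical methods section also refers to a separate, approved analysis plan. That plan was not available for this check.

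**The concern.** Chi-square and Fisher's exact test are for categorical data. Of the unadjusted tests listed, one-way ANOVA is the only one that suits a continuous score across seven arms, and it takes no covariate. Where the protocol does describe adjustment, it admits only stratification factors, and only after an imbalance has been seen.

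Two things follow for WHO QoL and WURSS. The day-0 value of the same instrument, usually the obvious covariate for the day-7 value, has no stated place in the model. And whether any adjustment is made depends on looking at the baseline data, so the model is not fixed in advance.

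What is at stake is precision, not validity. The value of that precision depends on the size of the arms. The Abstract (Trial Status) reports about 470 recruits by July 03, 2020, against 7 × 520 = 3,640 if every arm were to reach the indicative size.

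**Working it through.** **1. The protocol's own figure.** The Sample size section (item 14) assumes 50% against 60% negative at day 7 and says "at a significance level 5% and a power of 90%, a sample size of approximately 520 subjects in each group will be required". The Statistical methods section sets a two-sided test: "The two-sided p-value less than or equal to 0.05 will be taken as significant". With pooled variance and no continuity correction:

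n = [1.96 × √(2 × 0.55 × 0.45) + 1.2816 × √(0.5 × 0.5 + 0.6 × 0.4)]² / 0.10² = (1.379 + 0.897)² / 0.01, which gives 519 per group.

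The stated 520 is reproduced. It rests on the binary laboratory outcome, so this point does not affect it. No sample size or power target is stated for WHO QoL or WURSS.

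**2. Variance of a pairwise group comparison.** Take the variance of the day-7 score as 1, with equal variance on day 0. Let rho be the day-0 to day-7 correlation. The protocol gives no value, so 0.3 to 0.7 is assumed.

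| Analysis | Factor | rho 0.3 | rho 0.5 | rho 0.7 |
|---|---|---|---|---|
| Day-7 score alone | 1 | 1.00 | 1.00 | 1.00 |
| Change from day 0 | 2(1 − rho) | 1.40 | 1.00 | 0.60 |
| Day-7 score adjusted for day 0 | 1 − rho² | 0.91 | 0.75 | 0.51 |

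The adjusted analysis has the smallest variance in every column.

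**3. Power.** For a pairwise contrast, two-sided 5%: power = Φ(d × √(n/2) / √(factor) − 1.96). The protocol's only standardised difference is 0.3, given for the clinical primary outcome. A value of 0.2 is added because it is about what 520 per group detects with 90% power (3.2415 × √(2/520) = 0.201).

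| n per arm | d | Day-7 alone | Adjusted, rho 0.3 | rho 0.5 | rho 0.7 |
|---|---|---|---|---|---|
| 520 | 0.3 | 99.8% | 99.9% | over 99.9% | over 99.9% |
| 520 | 0.2 | 89.7% | 92.2% | 96.1% | 99.5% |
| 150 | 0.3 | 74% | 78% | 85% | 95% |
| 67 | 0.3 | 41% | 44% | 52% | 68% |

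Worked entry, n = 150, d = 0.3: 0.3 × √75 = 2.598. Unadjusted, Φ(2.598 − 1.96) = 74%. At rho 0.5, Φ(2.598/0.866 − 1.96) = Φ(1.04) = 85%.

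The smaller arm sizes are assumptions. 67 is 470/7. About 150 carries the accrual forward: 470 over the 74 days from April 20 to July 03 is 6.35 per day; 470 + 92 × 6.35 = 1,054; 1,054/7 = 151. Both assume that all recruits are randomised equally to seven arms.

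**4. Against change scores.** At 520 per group and d = 0.2, power on the change score is 77.8%, 89.7% and 98.6% at rho 0.3, 0.5 and 0.7. The adjusted figures are 92.2%, 96.1% and 99.5%. At rho 0.7 the variance advantage over the change score is 1 − 0.51/0.60 = 15%, against 49% over the day-7 score alone.

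**The case against.** A reader might infer that the baseline score is never used, and that one-way ANOVA is the assigned test for these two scores. The text supports neither. The list of methods covers all secondary analyses. Other continuous secondary variables, such as hospital days and durations of oxygenation or ventilation, have no day-0 value and could be what ANOVA is meant for. ANOVA on change from day 0 would use the baseline. Multiple regression is the first method in the same list, its covariates there are not named, and the limit to stratification factors stands in the preceding sentence. A model with the day-0 score is therefore not forbidden. All of this stands.

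A second inference would be that the trial loses substantial power. That depends on an assumed correlation and on arm size. At 520 per group and d = 0.3 the gain is negligible; at rho 0.3 it is 2 to 4 points in the other scenarios. The 150-per-arm figure extrapolates accrual, although the protocol foresees at least three more months, plans to drop arms, and has a non-randomised cohort. This stands too.

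Unadjusted ANOVA is unbiased under randomisation and controls the type I error, and its confidence intervals already allow for chance baseline differences. These are secondary outcomes with no stated power target.

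The objection that the matter belongs to the analysis plan stands only in part. The plan may well contain a baseline-adjusted model. But the protocol is not silent: it names tests and states a covariate rule, and that rule does not provide for the day-0 score and makes adjustment conditional on what is observed.

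**Conclusion.** The point holds as an efficiency improvement, not as an error that biases a result. The protocol collects the day-0 scores, names a covariate-free test among its group comparisons, and states one covariate rule, which covers only center and age and applies only on observed imbalance.

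Adjustment for the day-0 score would cut the variance of the day-7 comparison by 9%, 25% or 49% at rho 0.3, 0.5 or 0.7. The power gain runs from nothing of note (520 per group, d = 0.3) through about 2 to 10 points (520 per group, d = 0.2) to about 4 to 21 points at an extrapolated 150 per arm with d = 0.3. These figures rest on the assumed correlation, equal variances on the two days, and a comparison with the day-7 score alone. The gain over a change-score analysis shrinks as rho rises.

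**What to change.** In the Statistical methods section, state that WHO QoL and WURSS will each be analysed by a linear model of the day-7 score on randomised group and the day-0 score of the same instrument, with the stratification factors center and age. Say that the model is fitted whatever the observed baseline balance, that it replaces one-way ANOVA for these two outcomes, and that adjusted mean differences with 95% confidence intervals will be reported. Amend the covariate sentence so that it no longer restricts these two outcomes to stratification factors. If the separate analysis plan already specifies such a model, bring the protocol sentence into line with it.

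The cost is about one sentence in the protocol and a matching entry in the analysis plan. The day-0 scores are already collected, and SPSS, the named software, fits the model. No extra visits, data or participants are needed.
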